### Measures

Various measurement instruments are used to investigate the primary hypothesis of parent reported change in child externalizing and internalizing symptoms. and the secondary hypotheses testing various outcomes such as change in proximal family relational outcomes, and other more distal child and parent level outcomes, including moderators, mediators and background factors. An overview of assessment instruments is displayed in Table 1.

**Table 1 Tab1:** Measurement instruments

Measures	Respondent	Level outcome	T1	T2	T3	T4	Weekly assessed
ECBI	Parent	Child	x	x	x		
RCADS-P	Parent	Child	x	x	x		
SDQ-P	Parent	Child	x	x	x		
SRQ	Parent	Child	x	x	x		
Kid-KINDL	Child	Child	x	x^1^			
PAFAS	Parent	Relational	x	x	x		
FRQ	Parent	Relational	x	x	x		
PAB	Parent	Relational	x	x	x		
MaaP-SF	Parent	Parent	x	x	x		
PSS	Parent	Parent	x	x	x		
SWLS	Parent	Parent	x	x	x		
HSCL-10	Parent	Parent	x	x	x		
LES	Parent	Parent	x	x	x		
BioM	Child	Child	x	x^1^			
BioM	Parent	Parent	x	x^1^			
PRQ	Practitioner	Service & Intervention	x	x			
FidQ	Practitioner	Intervention					x
WAI-S	Practitioner	Intervention		x			
WAI-S	Parent	Intervention		x			
UserSQ	Parent	Intervention		x			
RBD	Registers	Child				x	

The parent questionnaires take approximately 20 min to complete. Parents receive 200 NOK (approximately 20 USD) as compensation for the time spent completing the questionnaires and providing hair samples. Instruments with positively formulated items are strategically interspersed among the instruments with negatively formulated items.

For the primary outcome on externalizing problems at T1-3, we will use the parent reported Eyberg Child Behavior Inventory intensity scale (ECBI; [60]) which assesses frequency of children’s externalizing symptoms. For the primary outcomes on internalizing symptoms, we will use the Revised Child Anxiety and Depression Scale parent version (RCADS-P; [61]). In addition, as this is a community level sample with heightened, but not clinical level, symptoms, and may include both children with externalizing and/or internalizing problems, we include the Strengths and Difficulties Questionnaire parent report (SDQ-P). The 20-item total problem scale from the SDQ-P, which assesses multiple correlates of internalizing and externalizing symptoms in children, is included as a primary outcome [62].

Secondary child level outcomes will be assessed utilizing the following instruments at T1-3: For the parent reported child behaviors we use a school refusal questionnaire (SRQ) that has been constructed for the SPARCK project to tap parent reported child school refusal behaviors. The items are reported on a 5-point scales ranging from “Very rare” to “very often”. For example, “In the last month, how often have your child said that he/she doesn’t want to go to school”. For child self-report of subjective quality of life, children aged ≥ 7 years (or who turn seven within that specific year) will fill out the 24-item Kid-KINDL [63] on paper-and-pencil version assessed at T1 and at four weeks past T2.

Secondary parent reported family outcomes at T1-3: The Parenting and Family Adjustment Scales (PAFAS) is used to assess parenting practices and family interactions and relationships [64]. A 7-item family routines questionnaire (FRQ) was purposefully developed for the current trial. This instrument aims to gauge both the frequency and extent of cooperation within everyday routine scenarios. The questionnaire comprises three items focused on the frequency of daily routines, employing a 5-point Likert scale that spans from "completely disagree" to "completely agree." For instance, “My child repeats the same procedures every night before going to bed”, and “My child and I share one meal at least once daily”. Additionally, the family routine questionnaire encompasses four items designed to evaluate the degree of cooperation prevalent in daily routines, assessed on 7-point scales ranging from “Very bad” to “Very good”. A questionnaire on family accommodation has been systematically developed to assess parental accommodation behaviors (PAB) in response to child difficulties. The questionnaire comprises 14 items, encompassing distinct dimensions of accommodation. Among these, five items pertain to parental accommodation behaviors within the context of daily family routines and four items examine parental accommodation within the realm of the parents' own life spheres, including work, social interactions, leisure activities, and sleep patterns. Moreover, the questionnaire incorporates five items targeting parental avoidant behaviors. For instance, respondents are asked to indicate the extent to which they permit their child to abstain from participating in activities commonly undertaken by children of comparable age.

For parent-level outcomes, several parent-reported instruments are assessed across T1-3. Me as a Parent, short-form (MaaP-SF; [65]) measures parental self-efficacy. The Perceived Stress Scale (PSS), consisting of 10 items, evaluates parents' subjective perception of stress [66]. Parents global perception of life quality is assessed with the Satisfaction With Life Scale (SWLS; [67]). Psychological distress is assessed using the 10-item version of the Hopkins Symptom Checklist (HSCL-10; [68]). Parents exposure to positive and negative life events in the last year is captured with the Life Events Scale (LES; [69]). Various background factors such as demographics and social and economic resources, family constellation etc., will be reported by parents and obtained at T1 and T3 assessments.

Biological markers of stress hormones levels (BioM), cortisol and dehydroepiandrosterone (DHEA), will be collected from 2 cm scalp hair samples collected at T1 and four weeks after the parent web-based T2 assessments, as 2 cm hair scalp samples contain approximately 8 weeks of biological material. The target child and the primary caretaker provide the hair samples. If the intervention is delayed in the study conditions, hair samples will be collected 4 weeks after week 25. Hair samples are self-sampled, wherein parents are provided with hair sampling kits encompassing all the required materials and comprehensive instructions elucidating the process of segmenting and cutting the hair samples. If parents face difficulties with the collection of hair samples, they are instructed to seek assistance or contact NUBU study coordinators.

In both study conditions we digitally assess intervention content, practitioner characteristics, and service-related details as reported by practitioners. For practitioners in the UC condition 1, a practitioner report questionnaire (PRQ) has been developed to evaluate therapist background, service-related aspects, educational background, training in EBIs, and counselling experience etc. Moreover, PRQ at T2 evaluates whether an EBI were provided and what intervention components that were given to families in the condition 1 counselling. Parallel assessments are conducted for the condition 2 SPARCK practitioners on practitioner and service characteristics. Additionally, condition 1 practitioners supply information regarding intervention administered to condition 1 families, outlining if a standardized or EBI has been provided, intervention components, session frequency, dosage, recipients, and targeted issues. Condition 1 practitioners provide their background and service-related details at intervention onset, whereas intervention specifics are reported upon completion or by week 25. In contrast, condition 2 practitioners complete a web-based fidelity questionnaire (FidQ) designed and optimized during the SPARCK development phases, detailing recipients, intervention strategies employed, pedagogical tools used, client engagement, and parental assessment of Goals in intervention. This SPARCK questionnaire is completed weekly after each session. Condition 2 practitioners report service and practitioner characteristics at project start-up. Parent and practitioner reported working alliance will be assessed using the 12-item Working Alliance Inventory – short form (WAI-S; [70]). Parent reported satisfaction with intervention will be reported with a User satisfaction questionnaire (UserSQ) adapted from the Family satisfaction survey [71]. UserSQ contains 5-items assessed on 5-point Likert scales ranging between “Not correct” and “Correct all the time”. Finally, register outcomes on child referrals to mental health outpatient specialized services and CWS services (RBD) will be collected two years after T3 follow-up assessments.

### Data analyses

The effect of the SPARCK vs UC will be indicated through a group (between) by time (within) interaction effect in a mixed effect repeated measures design. Respondents will be included in the analysis if they are assessed at T1 and randomized following the intention-to-treat principle. Missing data at any timepoint will be handled with appropriate missing data techniques depending on the type of data and missing data patterns. For the parent and practitioner-reported web-based questionnaires, completion of all instrument items is mandatory, ensuring that there will be no missing data at the item level. With an expected weak effect size of f = 0.1, GPOWER 3.1 estimates the necessary n to detect group by time interaction with 80% power to be 164, but this is based on no design effects and no dropout. Assuming a therapist intraclass correlation of 0.08 [72], with 4 cases per therapist, the design effect is 1.24, giving an effective n of 80% of the nominal n. Correcting for design effects and dropout the needed effective sample size is 252. Further, a dropout of 20% can be assumed. Forty-nine potential SPARCK practitioners across 24 municipalities have already committed to contribute. With four cases per SPARCK practitioner and four control cases, the total potential N is currently 392. We are thus within reach of a planned 20% safety margin to account for practitioner and participant drop-out.

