We posit several hypotheses to guide the investigation of SPARCK. More specifically, our primary hypothesis is: H1: Children of parents receiving SPARCK will exhibit lower levels of internalizing and/or externalizing symptoms compared to those who receive UC at a) the end of the intervention and b) 6 months post-intervention. Our secondary hypotheses are: H2: Parents in the SPARCK condition will demonstrate better parenting practices, self-efficacy, and less parental stress than parents in the UC condition at a) the end of intervention and b) 6 months post-intervention; and H3: The effect of SPARCK on child symptoms is mediated by changes in parenting practices; H4: Children (≥ 7 years) and parents in the SPARCK condition will report better subjective quality of life than children (≥ 7 years) and parents in the UC condition; H5: Among those who display abnormal blunted or elevated stress hormone levels as indicated by cortisol and DHEA at pre-intervention, children and parents in SPARCK will be more likely to change towards normative levels at post-intervention than those who receive UC; H6: Children in the SPARCK condition will display lower levels of school refusal than children in the UC condition at a) the end of intervention and b) 6 months post-interventions; and H7: Children in the SPARCK condition will be less likely to be referred to child and adolescent outpatient clinics (Norwegian abbreviation: BUP) or have contact with the Child Welfare Services (CWS) in the following two years compared to children in the UC condition.

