## Methods

### Study design

This study is a two-armed parallel group randomized controlled effectiveness superiority trial with assessment of key variables at pre-, post-, and six-months follow-up. Participants (i.e., parents) will be allocated either to receive SPARCK or UC.

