**Fig. 1 Fig1:**
[figure not shown]
Flow of participants in the study

Randomization will be performed using an online database hosted by the external provider, Klinforsk, at the Norwegian University of Science and Technology [59] www.klinforsk.no. Accordingly, the allocation sequence will be blinded for researchers, study personnel and practitioners working in the municipalities. Stratified pairwise randomization will be used, meaning that pairs of children/familieswill be recruited from each municipality after which one child/family will be randomized to receive SPARCK and the other to UC. If a second case is not recruited within a four-week period, a single case block randomization backup solution will be used to prevent prolonged delays for the first recruited child/family. In case of such single case randomization, the block size will be blinded for researchers, study personnel and practitioners in the municipalities, to prevent bias in the recruitment process. Participants will be randomized after signing a written informed consent and completing the pre-assessment.

While blinding is difficult or even unfeasible in human-delivered interventions like SPARCK and in the UC condition interventions, efforts have been made to mask participants from knowing which study condition they belong to. All information materials use neutral language such as "condition 1" (UC) and "condition 2" (SPARCK), and municipal recruitment personnel are trained not to provide any biased information to participants. However, it may be challenging to maintain masking during and after receiving the intervention, and participants may figure out which study condition they belong to if practitioners reveal the study condition.

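### The treatment effect is stated, and the trial sized, as a non-directional group-by-time interaction that tests H1a and H1b only jointly; baseline-adjusted T2 and T3 differences should be named as the primary estimates

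*Protocol article*

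**What the plan says.** All references are to the protocol article.

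- **Hypothesis.** Under Aims and research questions, H1 predicts lower internalizing and/or externalizing symptoms in the SPARCK arm "compared to those who receive UC at a) the end of the intervention and b) 6 months post-intervention". These are two directional statements, each about one time.
- **Design.** Study design gives "assessment of key variables at pre-, post-, and six-months follow-up", so there are three occasions: T1, T2 and T3.
- **Analysis.** Data analyses states: "The effect of the SPARCK vs UC will be indicated through a group (between) by time (within) interaction effect". It names no arm difference at T2 or T3, and does not say how T1 enters the model.
- **Sample size.** The same section continues "With an expected weak effect size of f = 0.1" and reports that the software "estimates the necessary n to detect group by time interaction with 80% power to be 164", adding that "this is based on no design effects and no dropout". Alpha and the correlation between repeated measures are not given.
- **Timing of T1.** Participants, recruitment, and randomization states: "Participants will be randomized after signing a written informed consent and completing the pre-assessment".

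**The concern.** The hypothesis and the stated indicator of effect do not match. H1a and H1b each ask whether symptoms are lower under SPARCK at a given visit. A three-occasion interaction asks whether the two arms' profiles differ in any way over T1, T2 and T3. It has no direction, and it can be significant because of one visit alone or because an early benefit reverses. A significant result could therefore be reported as support for H1 when one of its two parts, or its direction, has not been shown.

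The second issue is precision. T1 is measured before allocation, so the arms can differ there only by chance. A model that estimates T1 means separately by arm carries that chance difference into every comparison of change. Using T1 as a covariate, or constraining T1 means to be equal, removes much of this noise from data already collected.

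**Working it through.** **Inputs.** From the article: two arms, 1:1 allocation, three occasions, f = 0.1, 80% power, N = 164. Assumed because not stated: alpha 0.05 (two-sided for contrasts), correlation ρ = 0.5 with compound symmetry, sphericity. I also show ρ = 0.3 and 0.7.

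**1. Reproduce 164.** For a within-between interaction with m occasions and two arms, λ = f²·N·m/(1−ρ), df1 = m−1, df2 = (N−2)(m−1). With m = 3, ρ = 0.5, N = 164: λ = 0.01 × 164 × 3/0.5 = 9.84 on 2 and 324 df, power 0.805. N = 162 gives 0.7998. At ρ = 0.5, two occasions need 200 and four need 138. Two occasions at ρ = 0.6 give 160, near but not equal. So 164 is the three-occasion, 2-df test.

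**2. Put f on the outcome scale.** For arm differences (0, d, d) over T1–T3, f² = d²/18, so d = √0.18 = 0.424 SD. The same f gives (0, 0.245, 0.490) SD for a gradual effect and (0, 0.424, 0) for an effect at T2 only.

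**3. What a significant result shows (N = 164, ρ = 0.5).** For differences in change (δ2, δ3), λ = (N/4)·(δ2² + δ3² − δ2δ3)/[1.5(1−ρ)], where 1.5(1−ρ) = 0.75.
- Sustained 0.424 SD: 41 × 0.18/0.75 = 9.84, power 80.5%.
- Benefit of 0.3 SD at T2, harm of 0.3 SD at T3: 41 × 0.27/0.75 = 14.76, power 94%.
- By simulation, with an effect at T2 only, the test was significant in about 81% of trials, and in 94% of those the T3 contrast was not significant. With a gradual effect, the T2 contrast was not significant in about half of the significant results.

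**4. Precision at one visit.** The variance factor is 2(1−ρ) for change from T1 and 1−ρ² with T1 as covariate, a ratio of (1+ρ)/2. That is 0.75 at ρ = 0.5 (25% lower) and 0.85 at ρ = 0.7 (15% lower). For a sustained effect at N = 164:
- change: SE = √(4 × 1.00/164) = 0.156, power 77%;
- adjusted: SE = √(4 × 0.75/164) = 0.135, power 88%.

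**5. Like for like, 2 df against 2 df.** For the adjusted test, λ = (N/4)·δ′S⁻¹δ, where S has 1−ρ² on the diagonal and ρ−ρ² off it. N is what the plan's method gives at each ρ.

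| ρ | N | Interaction, T1 free | Adjusted, sustained | Adjusted, gradual | Adjusted, T2 only |
|---|---|---|---|---|---|
| 0.3 | 228 | 80.3% | 97.6% | 95.8% | 87.8% |
| 0.5 | 164 | 80.5% | 93.8% | 91.7% | 85.2% |
| 0.7 | 98 | 80.1% | 88.5% | 86.7% | 82.5% |

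For the reversal in step 3 at ρ = 0.5, the adjusted 2-df test also has 94% power. Adjustment improves precision but does not give direction; only the visit-specific contrasts do that.

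**6. Single-visit adjusted contrasts against the 2-df interaction (sustained effect).**

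| ρ | Full alpha (0.05) | Alpha 0.025 per visit | 2-df interaction |
|---|---|---|---|
| 0.3 | 91.7% | 86.4% | 80.3% |
| 0.5 | 87.7% | 80.8% | 80.5% |
| 0.7 | 82.9% | 74.5% | 80.1% |

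With a gradual effect at ρ = 0.5 and full alpha, T2 has 43.7% and T3 95.0%. If both visits must succeed at 0.05 under a sustained effect, power is about 79%.

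**The case against.** Several points on the other side are right.

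- **The df and the handling of T1 are not stated.** The 2 df are inferred from the sample size, and a sample-size shortcut does not fix the analysis model. A model with T1 means constrained equal also expresses its effect through group-by-time terms, and the article does not exclude it. The precision loss is therefore conditional on T1 means being left free.
- **A reader might infer that the plan tests neither part of H1 and yields no estimate at T2 or T3.** The article does not support that. Under randomisation, the interaction null is the joint null of H1a and H1b, so both are tested together. With time as a factor, the same model gives unbiased differences in change at T2 and T3.
- **A reader might infer that chance T1 differences produce false positives.** They do not. They are part of the error variance, and the type I error stays nominal. The cost is precision.
- **An analysis plan not shown may name the contrasts.** That is possible. But the article does more than leave the matter open: it names an indicator of effect and sizes the trial on it, and that indicator does not match the hypothesis it serves.
- **Moving to two contrasts has a price.** With three primary instruments (ECBI, RCADS-P and SDQ-P, under Measures), one test each becomes two each, six in all. A 2-df gatekeeper followed by contrasts is a legitimate alternative.

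**Conclusion.** The point holds in limited form. The stated interaction, at the df that reproduce 164, does not separately establish lower symptoms at T2 or at T3 and has no direction. That mismatch does not depend on the power figures. The efficiency argument holds on the same 2 df for each effect pattern tried: from about 80% to 85–94% at ρ = 0.5, and to 83–98% over ρ = 0.3–0.7. It rests on the assumed alpha and correlation, on compound symmetry, and on T1 means being free by arm in the planned model.

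It would be too much to say that visit-specific contrasts always gain power over the interaction. They do so at ρ = 0.5 (88% against 80.5%) for a sustained effect at full alpha. Halving alpha leaves about 81%, and at ρ = 0.7 it turns into a loss. A baseline-adjusted average of T2 and T3 would reach 97% for a sustained effect, but only 48% for an effect at T2 only, and it answers neither H1a nor H1b. That figure is no measure of the gain here. The plan is valid as it stands; the change is worth making because it is nearly free and aligns the test with the hypothesis.

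**What to change.** In Data analyses, replace the interaction as the indicator of effect with the following:

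- The primary estimates are the SPARCK–UC differences at T2 (H1a) and at T3 (H1b), each with a 95% confidence interval.
- They come from a mixed model with arm-by-visit terms, with T1 as covariate or T1 means constrained equal across arms.
- State how alpha is handled across the two visits for each primary instrument: a split, a fixed order, both required, or a gatekeeper.
- The 2-df test may stay as a gatekeeper if it is baseline-adjusted and followed by these two contrasts.
- Check the sample size against the chosen rule, stating alpha and the assumed correlation.

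This takes about one paragraph and no new data. The downside is two contrasts per primary instrument, which need the alpha rule. Under an even split, the single-visit power advantage over the interaction is about nil at ρ = 0.5.

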### Data management

To ensure the security and privacy of sensitive information, we use the University of Oslo's Services for Sensitive Data (TSD) for all data storage and analysis. We use Nettskjema, also developed and operated by the University Information Technology Center, a TSD-integrated survey solution for collecting sensitive data. All study information, including participant identification keys and raw data, will be securely stored in TSD. Access to this information will be restricted to authorized personnel. Specifically, only study coordinators will have access to participant identification keys and raw data, while researchers will only have access to de-identified data. We will also implement measures to protect data confidentiality and integrity, including encryption of all data transfers and regular backups to safeguard against data loss. In the event of any breaches or unauthorized access, we will follow established protocols for reporting and responding to such incidents. Hair samples and paper questionnaires will be adequately secured and stored at NUBUs’ locations.

## Discussion

The SPARCK intervention is a novel intervention that requires empirical evidence about effectiveness in a randomized trial. The current study has the potential to make a significant contribution in this regard and to the understanding of how a preventive transdiagnostic intervention may perform in Norwegian regular care services.

The primary objective in this study is to test the effect of SPARCK when compared with standard care. Accordingly, the current study may shed light on how a transdiagnostic preventive intervention can yield favorable outcomes or not when compared to focal interventions in standard care typically more focal in scope aimed at delimited target groups. A related question is whether the inherent transdiagnostic and personalized feature of SPARCK may also enhance effectiveness by allowing for flexible tailoring of content to fit the specific needs of each family. If SPARCK yields treatment effects over and above standard care, SPARCK holds the potential to innovate the municipal frontline services with a flexible and effective parenting intervention that may reach a large user group in need of frontline support services. At the service level, the transdiagnostic feature of SPARCK is customized to a to a varied landscape of Norwegian municipal frontline services, which differ in size, resources, and organizational structure. In particular, municipalities in small and rural areas may lack resources that is required to implement multiple evidence-based interventions (EBIs) for specific problems. If proven effective, SPARCK can promote the frontline usability and delivery of effective intervention content to larger segments of end users, thereby supporting equity in care throughout Norway's heterogeneous municipal landscape.

The heterogeneity in end-users, services, and municipalities reflect the regular practice realities [73]. Currently, we have chosen to conduct an effectiveness study in a naturalistic setting, and not in a highly controlled efficacy-study, as performed in the SPARCK optimization cycles. However, this choice brings along some limitations regarding heterogeneity of child symptomatology when analyzing outcomes. This is a particularly relevant problem when analyzing outcomes from transdiagnostic interventions. For example, if children do not display comorbid internalizing and externalizing symptoms, the non-present symptom may statistically mask the effect on the symptom which is present. For example, if a child displays anxiety symptoms only, it is expected to observe a change primarily on anxiety symptoms but not, or only to a small degree, on conduct and depression symptoms. However, being a transdiagnostic intervention, the outcome is nevertheless measured as consisting of all three symptom domains. Thus, the heterogeneity in the sample may lead to an underestimation of treatment effects. In this regard, the design per se is not put up to explain for instance for which group of main symptoms SPARCK is better (or effective). Other and more general limitations will also apply in RCT, for instance which of the SPARCK components are effective for what groups or if SPARCK is effective in some services, but not others. However, mediation and moderation analyses in addition to the implementation part of the study (not described here) will hopefully contribute to shed light on such questions.

Another systematic difference between study conditions worth noting is the background training of the practitioners. For example, we use trained PMTO therapists to deliver the SPARCK condition. The PMTO therapist have previously undergone a 21-day training program including training in active teaching skills such as role play and problem solving, and clinical process skills. Thus, the SPARCK practitioners all possess some content and process skills that may have enabled them to learn the SPARCK material competently. On the other hand, practitioners in the UC condition may possess background training and process skills comparable with PMTO therapists, and the list of interventions supplied by the municipalities describing the potential UC interventions show that many UC practitioners indeed have undergone training in manualized interventions and EBIs. To monitor such potential differences between study conditions, we assess various practitioner backgrounds such as education, years with a relevant job, if they are specialists, training in any EBIs etc. in addition to counsellor alliance and the content delivered in UC.

Relatedly, another potential effect of conducting a randomized controlled effectiveness trial in naturalistic settings is that those who deliver the UC condition provide more and/or better interventions because of being observed in the study. Thus, the municipalities may have mobilized to provide “good enough” UC, which may also bias the results. In the SPARCK RCT design, we have less control over such factors.

We recognize that implementing a large-scale randomized study in regular care is resource demanding and often difficult, and that there are many potential pitfalls that may affect the risk of bias and in turn the knowledge base for which to conclude about effects. Thus, it has been pointed out that future research on family-based interventions should use robust designs, but also be based on a close cooperation between the scientific and the local environments. We answer this call for research anchored in both science, practice, and local communities. With a previously co-created and optimized intervention, we hope that this randomized effectiveness study, together with the implementation study, will contribute with findings that address the challenges related to effectiveness and successful implementation of parenting interventions for prevention of childhood mental health problems.

